**4.2 Inclusion criteria**

All inclusion criteria have to be fulfilled before patient enrolment into the study.

1. Male or female patients with ≥18 years of age
2. Suspected renal carcinoma limited to one kidney
3. Planned for a partial nephrectomy (PN)
4. Written informed consent, after detailed information by the investigator

**4.2 Exclusion criteria**

1. Patients with a chronic kidney disease (CKD), and a pre-operative glomerular filtration rate (GFR) < 60 ml min^-1^ 1.73^-1^ m^-2^
2. American Society of Anesthesiologists (ASA) status > III
3. Known contraindication and hypersensitivity to propofol, sufentanil, Xe, Iso or rocuronium
4. Severe pre-existing cardiac disease (New York Heart Association-Classification (NYHA)<III), acute coronary syndrome during the past 24 hours, hemodynamic instability or requirement of catecholamines
5. Severe respiratory disease (Forced expiratory volume in one second/ forced vital capacity (FeV1/FVC)<70% and FeV1<30%), severe respiratory insufficiency with a partial pressure of oxygen in arterial blood (PaO_2_)<60mmHg, or home oxygen therapy
6. Severe neurological disease
7. Increased intracranial pressure
8. Risk for malignant hyperthermia
9. Pregnant or breast-feeding woman
10. Legally incompetent patients
11. Refusal of consent
12. Concurrent participation in other interventional studies in the last 30 days
13. Language and communication difficulties during study information
14. People who are institutionalized by court or administrative order
15. Subjects with dependent/ employment relationship to the sponsor or the investigator

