**1.2 Rationale**

The noble gas xenon (Xe) is approved since 2005 in Germany and 2007 in Europe for clinical routine use as an inhalational anesthetic. It is used for balanced anesthesia together with opioids for adult American Society of Anesthesiologists (ASA) ≤III patients. Different experimental *in vitro* and *in vivo* models were able to demonstrate the neuroprotective and cardioprotective effects induced by Xe treatment [12-15]. Both pre- and post conditioning protocols were effective [16-17]. Nephroprotection by Xe was recently shown in an *in vivo* IRI model and *in vitro* model of glucose deprived injury in human tubular kidney cells [18-19]. Both studies found an increased expression of hypoxia inducible factor-1α (HIF-1α) in the Xe treated cells or kidneys of the animals [18-19]. The nephroprotective effect was abolished by inhibition of HIF-1α activity [18]. Further nephroprotective effects showed Pype et al. Xe-saturated cold storage solutions reduced the ischemia-reperfusion injury after 6 hours of cold ischemia in a rat model of renal transplantation [20]. Animals with Xe-treated kidneys showed better creatinine-clearance after 7 and 14 days and decreased excretion of albumin in urine, which shows the tubular injury [20]. Clinical data from our study group revealed a better renal function in patients undergoing cardiac surgery after Xe anesthesia [21]. Furthermore, we could show that IRI on cardiac surgery patients leads to an enhanced release of macrophage migration- inhibiting factor (MIF) in serum. MIF was associated with an enhanced antioxidative capacity and less postoperative renal failure [22]. Therefore the influence of Xe compared to isoflurane on MIF should be examined in the present study. Beside the experimental organ protective effects, Xe is an effective anesthetic with favorable hemodynamic properties with blood pressure stability and low heart rates [10-11]. Other anesthetics like isoflurane, desflurane, sevoflurane and propofol usually show low blood pressures; with the need of catecholamines during anesthesia. Both low mean arterial pressures as well as the vasoconstrictive drugs like norepinephrine have additional negative influence on the renal function. This could lead to a beneficial risk-benefit ratio for Xe.

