**4.4 Patient exclusion criteria and procedure**

**4.4.1 Reasons for premature study-exclusion and termination of the investigational product administration**

- Patient safety has the first priority. A patient will be excluded before intervention, if an exclusion criterion appears after patient inclusion- but before intervention- (e.g. change of the surgical technique, acute patient deterioration, etc.). Patient data will receive a screening number and will be stored in a locker.
- A retrospectively noticed deviation from the inclusion or exclusion criteria (after the beginning of the intervention) will induce a study drop out. Depending on the time-point, the patient will receive a standard anesthesia and the data management will excluded the patient.
- Consent withdrawal: Patients can withdraw whenever they want. All collected data until the withdrawal time-point as well as the randomization group have to be filed. The patient has to be informed, that already collected data will be used further on.
- Severe adverse events (SAE) and suspected severe adverse reactions (SUSAR), which prohibit further study conduction.
- Adverse events (AE) and adverse reactions (AR), which seem to be hazardous for the physical and psychological health of the patients, as evaluated by the principle investigator.
- Technical difficulties and required modifications of the investigational product administration device.

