**5 Individual course of study**

**5.1 Verification of the inclusion- and exclusion criteria**

Verification of the inclusion- and exclusion criteria of potential study-patients (screening) will be conducted according to a predefined checklist: All patients meeting the inclusion criteria: Suspected renal carcinoma limited to one kidney, planned PN and age of ≥18 years will already be informed by the colleagues of the Urology Department. An investigator will visit them if they are interested in study participation. The investigator will inform the patients about the individual risk and benefit of this study and evaluate the exclusion criteria. The patients will receive a patient information and ample of time for their decision to participate in this study. A screening log will be kept, where all eligible patients have to be documented. The enrolled patients will additionally be documented in this screening log. If a patient is not enrolled in this study, then at least 1 exclusion criterion has to be documented. Within the verification of the inclusion / exclusion criteria, the investigator has to document if the patient has participated in another clinical trial within the prior 30 days. The patient will be informed that he is not allowed to participate in further clinical trials, as this bears unpredictable risks for the patient.

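### Exclusion criterion 4 contradicts itself: it is labelled severe cardiac disease, but its bracket (NYHA <III) describes the milder classes

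*Protocol*

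**What the plan says.** Protocol section 4.2 (Exclusion criteria), criterion 4, opens with "Severe pre-existing cardiac disease (New York Heart Association-Classification (NYHA)<III" and then adds further grounds for exclusion: "acute coronary syndrome during the past 24 hours, hemodynamic instability or requirement of catecholamines". Criterion 2 of the same list excludes "American Society of Anesthesiologists (ASA) status > III".

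Section 5.1 says how the criteria are applied: "Verification of the inclusion- and exclusion criteria of potential study-patients (screening) will be conducted according to a predefined checklist". It also requires at least one exclusion criterion to be documented for a patient who is not enrolled.

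Section 4.4.1 gives the consequence of an error found later: "A retrospectively noticed deviation from the inclusion or exclusion criteria (after the beginning of the intervention) will induce a study drop out". Section 4.4.4 provides for replacing patients excluded after randomization.

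**The concern.** The words and the operator in criterion 4 point in opposite directions. The label excludes severe heart disease, while the bracket that defines it selects the mild end of the scale. An entry criterion should lead two careful readers to the same decision on the same patient, and this one does not.

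Two things are at stake. The first is safety: cardiac status bears on who should receive the study anesthetic, and a criterion meant to protect patients should not rely on staff recognizing that its sign looks wrong. The second is the status of enrolled patients. Someone who follows the label can enrol a class I or II patient who breaches the bracket as printed. Someone who follows the bracket can enrol a patient whom the label was meant to keep out. In either case the patient can later be called an eligibility deviation under section 4.4.1, depending on which half the checker reads.

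**Working it through.** No arithmetic applies, and the protocol gives no figure to reproduce. The check compares the criterion with its own label, with the rest of the list and with the rest of the protocol.

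**1. The bracket read literally.** The protocol does not define the NYHA scale. On the standard scale, class I is the mildest and class IV the most severe. The condition NYHA <III is then the set {I, II}, and classes III and IV fall outside it.

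**2. The bracket against the label.** The label requires the excluded set to sit at the upper end. The protocol does not say where that end starts, so two readings are set out below. They are illustrations only, and neither is proposed.

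| NYHA class | Bracket as printed | Label, if III and IV count as severe | Label, if only IV counts as severe |
|---|---|---|---|
| I | excluded | not excluded | not excluded |
| II | excluded | not excluded | not excluded |
| III | not excluded | excluded | not excluded |
| IV | not excluded | excluded | excluded |

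Under the first reading the printed bracket disagrees with the label for all four classes. Under the second it disagrees for three and agrees for class III. Label and bracket conflict under both, but the extent depends on a cut-off that the protocol does not give.

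**3. The other inequalities in the list.** ASA is also an ordinal scale on which higher is worse, and criterion 2 excludes the grades above III. Section 1.2 agrees with that direction: "It is used for balanced anesthesia together with opioids for adult American Society of Anesthesiologists (ASA) ≤III patients". The less-than signs in criteria 1 and 5 (GFR below 60, FeV1/FVC below 70%, FeV1 below 30%, PaO2 below 60 mmHg) are all on scales where lower is worse, so they point the right way. NYHA is the only graded scale in the list whose sign runs against its meaning, so the sign cannot be explained as a house convention.

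**4. Possible repair elsewhere.** NYHA appears nowhere else in the protocol. Section 5.1 refers to a checklist without showing how it words the cardiac item.

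**5. Other criteria that limit the effect.** Whatever the bracket says, patients above ASA III, patients who are hemodynamically unstable and patients who need catecholamines are excluded. Some patients in NYHA III or IV would therefore still be kept out. The protocol does not make these criteria equivalent to a NYHA limit, so they narrow the gap without closing it.

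**The case against.** The strongest defence is that the intent to exclude severe disease is plain. A physician would have to let a bracket override the leading words in order to enrol class III or IV and turn away class I or II. The document is also presented as an English translation of a German protocol, so the sign may be a slip that exists only in the translation. Both points are fair. They lower the practical risk and limit what can be said about how patients were actually screened. They do not make the printed criterion consistent.

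A reader might also infer several stronger things that the documents do not support:

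- **That every patient with a NYHA class is misclassified.** This needs class III to be among the classes meant, which the protocol does not say.
- **That the trial admits the worst cardiac cases.** This is true of the bracket taken alone, but the ASA, instability and catecholamine criteria still remove some of them.
- **That the screening checklist carries the reversed sign.** Its content is not shown.
- **That affected patients are forced out of the analysis.** Section 4.4.1 makes them drop-outs, but section 9.2 includes everyone randomized, so their removal is not settled.
- **That the variance of the GFR decline changes.** No figure in the protocol supports this.

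**Conclusion.** The point stands as an internal contradiction in an operative, safety-related entry criterion. As printed, the bracket excludes the milder NYHA classes and does not by itself exclude III and IV, contrary to its label, and no other section resolves the conflict. Eligibility, and deviation status under section 4.4.1, depend on which half is followed.

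The effect cannot be put in patient numbers. With 25 patients per group (section 9.1), one patient is 1/25 = 4% of a group. That shows only how much a single patient weighs and says nothing about how many are affected. The sample size calculation and the planned analysis method do not use this criterion.

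The conclusion rests on the standard ordering of the NYHA classes and on the English text as printed. Whether the operative German text has the same error is unknown.

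**What to change.** The sponsor should compare criterion 4 with the German original and reconcile the label with the operator. The criterion should then list the NYHA classes it means, including whether class III is among them, so that no inequality has to be interpreted. That choice belongs to the sponsor's clinicians, and the documents do not settle it. The same wording should go into the screening checklist used under section 5.1.

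If only the translation is wrong, correcting the translation is enough. If the German text or the checklist has the same sign, patients already screened should be checked against the confirmed criterion and any eligibility deviations identified.

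The text change is very small. If the operative protocol is affected, section 12.4 requires a written, reasoned and signed modification, and approval if it counts as substantial. The re-check would mean going through the screening log, where enrolled and non-enrolled patients are recorded.

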**4.4 Patient exclusion criteria and procedure**

**4.4.1 Reasons for premature study-exclusion and termination of the investigational product administration**

- Patient safety has the first priority. A patient will be excluded before intervention, if an exclusion criterion appears after patient inclusion- but before intervention- (e.g. change of the surgical technique, acute patient deterioration, etc.). Patient data will receive a screening number and will be stored in a locker.
- A retrospectively noticed deviation from the inclusion or exclusion criteria (after the beginning of the intervention) will induce a study drop out. Depending on the time-point, the patient will receive a standard anesthesia and the data management will excluded the patient.
- Consent withdrawal: Patients can withdraw whenever they want. All collected data until the withdrawal time-point as well as the randomization group have to be filed. The patient has to be informed, that already collected data will be used further on.
- Severe adverse events (SAE) and suspected severe adverse reactions (SUSAR), which prohibit further study conduction.
- Adverse events (AE) and adverse reactions (AR), which seem to be hazardous for the physical and psychological health of the patients, as evaluated by the principle investigator.
- Technical difficulties and required modifications of the investigational product administration device.

**4.4.2 Time-point of patient drop out/ cessation of study treatment**

Each patient may be excluded from this study at any time. If any of the above mentioned condition occurs, the patient will be immediately excluded. If this occurs during the administration of the study-treatment, this will be terminated and replaced by a standard anesthetic. The patient will be treated according to his medical need.

**4.4.3 Documentation of the time-point and kind of patient exclusion**

All data until exclusion from the study will be collected and documented. The reason and the exclusion time-point will be documented on a special CRF sheet. The investigator is obliged to name the main reason for exclusion. The sponsor has to be notified within <24 hours in case of SAE/ SUSAR. The sponsor will inform the regulatory body and the ethic committee about the SAE/ SUSAR if necessary.

**4.4.4 Replacement of excluded patients**

After randomization excluded patients will be replaced.

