**9.2 Patient selection for inclusion into the analysis**

All randomized patients will be included in the analysis.

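### The protocol excludes and replaces patients after randomization and requires no GFR sampling from them afterwards, which conflicts with its commitment to analyse all randomized patients by intention to treat

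*Protocol*

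**What the plan says.** Protocol section 4.4.1 lists the grounds for leaving the study. Besides consent withdrawal and exclusion before the intervention, they include SAEs and SUSARs, AEs and adverse reactions judged hazardous, and "Technical difficulties and required modifications of the investigational product administration device". On eligibility errors found late it says "A retrospectively noticed deviation from the inclusion or exclusion criteria (after the beginning of the intervention) will induce a study drop out", and that "the data management will excluded the patient".

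The consequences follow in the next subsections:

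- Section 4.4.2: "If any of the above mentioned condition occurs, the patient will be immediately excluded". Ending the study anesthetic is a further step, taken if the event falls during administration.
- Section 4.4.3: "All data until exclusion from the study will be collected and documented".
- Section 4.4.4: "After randomization excluded patients will be replaced".
- Section 4.4.5: excluded patients receive ordinary care. A final examination is recommended to those who withdraw.

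Section 12.1 adds that study participation ends when harm to the patient threatens or occurs, whatever the cause.

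On analysis, section 9.2 states "All randomized patients will be included in the analysis". Section 9.3 makes the primary analysis intention to treat, with imputation left to a statistical analysis plan, and section 9.4 repeats intention to treat for data that remain missing.

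The primary endpoint (sections 2.2 and 7.1.2) is baseline GFR minus the lowest GFR within the first seven postoperative days.

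**The concern.** Section 4.4 treats stopping the study anesthetic and leaving the study as one event. Followed as written, it takes randomized patients out after their allocation is known to the anesthesia team and puts others in their place. Section 9 promises the opposite population.

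Two things are at stake. The first is who enters the primary comparison: a site could fill each arm with 25 patients who got through the study anesthetic and treat the excluded ones as gone. The second is whether the endpoint exists for the excluded. A nadir over seven days needs the daily samples. A patient excluded during anesthesia has no postoperative study sample required. One excluded on day 2 has a nadir over a shortened window, which can only understate the decline.

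The grounds for exclusion are not neutral. Reactions and device problems arise from giving the study treatment. Under sections 7.2 and 8.3 every clinically significant laboratory value counts as an AE, and section 7.1.3 lists creatinine among the daily safety data. A marked fall in renal function, which is the outcome under study, could therefore itself be a ground for exclusion.

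**Working it through.** **Step 1. The rules side by side.**

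| Question | Section 4.4 | Section 9 |
|---|---|---|
| Is a patient with a late-found eligibility deviation in the analysis? | No: excluded by data management (4.4.1) | Yes: all randomized (9.2) |
| Is a patient excluded for an SAE, hazardous AE or device problem in the analysis? | Not stated; excluded from the study and replaced (4.4.2, 4.4.4) | Yes (9.2, 9.3) |
| Is GFR measured after exclusion? | Not required (4.4.3, 4.4.5) | Needed for the nadir, otherwise imputed (9.3) |

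The first row is a direct contradiction. The second is a gap: no section says whether a replaced patient stays in the analysis set. The third leaves the endpoint dependent on data that nobody is told to collect.

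**Step 2. Does the sample size need replacement?** Inputs from section 9.1: 23 per group required, 10% dropout expected, 25 per group planned.

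- Inflating for dropout: 23 / (1 − 0.10) = 25.6, so 26. The stated 25 is one patient short of that and reproduces to within rounding.
- Expected completers without replacement: 25 × 0.90 = 22.5 per group, against 23 required.
- If excluded patients are also replaced until 25 completers remain: 25 / 0.90 = 27.8, so 28 per group and 56 in total. Section 9.2 would then require 56 in the analysis, while section 9.1 plans 50.

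The allowance for dropout already covers the loss, so replacement compensates for it a second time.

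**Step 3. How large could bias be if the excluded patients were dropped?** The documents give no exclusion rate by arm and no outcome for excluded patients, so everything here is assumed. Let e₁ and e₀ be the excluded shares in the two arms. Let D be the amount, in SD, by which the mean decline of excluded patients exceeds the mean of all patients randomized to their arm, taken as equal in both arms. The mean of those retained is then lower by e·D / (1 − e), and

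bias = e₁·D / (1 − e₁) − e₀·D / (1 − e₀).

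With a true effect of zero and 25 analysed per arm, the standard error of the difference is √(2/25) = 0.283 SD. The two-sided type I error at nominal 5% is 1 − Φ(1.96 − bias/0.283) + Φ(−1.96 − bias/0.283).

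| e₁ vs e₀ | D | Bias (SD) | Type I error |
|---|---|---|---|
| 10% vs 10% | any | 0 | 5.0% |
| 15% vs 5% | 0.5 | 0.088 − 0.026 = 0.06 | 5.6% |
| 15% vs 5% | 1.0 | 0.176 − 0.053 = 0.12 | 7.2% |
| 20% vs 5% | 1.0 | 0.250 − 0.053 = 0.20 | 10.7% |
| 20% vs 5% | 1.5 | 0.375 − 0.079 = 0.30 | 18.2% |

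If the 1 SD excess is measured against retained patients instead, the 15% versus 5% case gives (0.15 − 0.05) × 1 = 0.10 SD. The figures are kept in SD units because the sentence in section 9.1 that links the SD to the target difference can be read in more than one way.

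**The case against.** The strongest reply is that replacement is a recruitment rule and intention to treat an analysis rule. The two coexist if replacements are additional and the excluded patients stay in the analysis set. That is right, so a reader who infers that sections 4.4.4 and 9.2 can never both be followed goes too far. But the protocol nowhere says that this is the arrangement, and exclusion by data management in section 4.4.1 does not fit it.

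A reader might also infer that excluded patients certainly have no postoperative GFR. The documents do not say so. Later collection is not forbidden. Section 8.4 has patients with AEs observed until laboratory values normalize, section 9.4 fills gaps from source data where possible, and section 13.1.1 accepts laboratory print-outs from outside the study as source data. Some creatinine values may be recovered that way. Daily cystatin C, which the endpoint needs, is not assured.

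The link to treatment is possible, not shown. Both arms use the same ventilator (sections 3.2 and 6.2). The postoperative investigator is blinded (section 5.3), and section 4.4.1 gives the judgement on hazardous AEs to the principal investigator. Knowledge of the allocation therefore mainly concerns exclusions during anesthesia. Exclusion before the intervention is largely harmless if the envelope is still closed.

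Finally, imputation is left to a statistical analysis plan that is not at hand, and its adequacy cannot be judged here. What stands is that the exclusion and collection rules are fixed in the protocol, and imputation is a poor substitute for samples that could have been taken from inpatients.

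**Conclusion.** The point holds as a conflict within the protocol that needs to be resolved. Section 4.4 removes randomized patients and requires no endpoint measurement afterwards, section 9 counts them in, and for late-found eligibility deviations the two are directly opposed. This goes beyond missing detail, because the exclusion rule followed as written decides who is compared and whether the nadir is observed.

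No definite size of bias can be claimed. Bias needs exclusions that are related to outcome and differ between the arms. It is zero when they are equal in frequency and in kind, and about 0.12 SD with a type I error of about 7% under the assumed 15% versus 5% and a 1 SD excess. A reader might infer that xenon would be favoured by a fixed share of the target difference. That would require exclusions in the xenon arm only, a chosen excess decline and one particular reading of section 9.1. The documents support none of these assumptions.

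**What to change.** - In sections 4.4.1 to 4.4.3, separate stopping the study anesthetic from leaving follow-up. When treatment is stopped need not change.
- Require the scheduled creatinine and cystatin C sampling to day 7 or discharge for every patient whose envelope was opened, unless consent for follow-up is withdrawn.
- State in section 9.2 that all these patients are in the primary analysis, in the allocated group.
- Delete the exclusion by data management. Report late-found eligibility deviations and examine them in a sensitivity analysis.
- In section 4.4.4, limit replacement to patients lost before the envelope is opened, or state that replacements are additional and the excluded patients remain in the analysis set. The 25 per group already allows for about 10% dropout.
- Reconcile the wording in section 12.1 on ending study participation with these changes.

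The cost is an amendment of wording, a few more routine inpatient samples and possibly slightly fewer patients in the per-protocol analyses.
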